### Procedure

Within schools, all the parents of 4–5 and 10–11 year old children will be sent an invitation to join the study. Recruited parents will be those who return a signed consent form. Every school that has at least one consented child will be randomised to Intervention A, Intervention B or control using a 1:1:1 ratio, as described in the ‘randomisation of schools’ section.

Parents in the control group will provide the baseline data for the trial. They will not receive either intervention during the study period. They will be posted the study questionnaire soon after the study team receive their consent forms; the questionnaire consists of the outcome and explanatory measures. Parents in the intervention groups will receive the intervention by post. Those randomly assigned to the web-based version will additionally receive a follow-up email with website link, if an email address was obtained. The intervention period lasts four weeks and after this period has elapsed all parents in the intervention groups will be posted the study questionnaire. Parents will be asked to complete and return the questionnaire to the study office in the provided postage-paid envelope. In the majority of cases, the study team will obtain the child height and weight measurements from the NCMP. All parents and children will be followed up at 12 months after the first day of the intervention; parents will be sent the study questionnaire to complete and return to the study office, and the children will be measured for height and weight by the study team, usually at school.

A favourable ethical opinion was obtained from National Research Ethics Service, Committee North East - Newcastle and North Tyneside 2: reference 12/NE/0409.

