### Randomisation of schools

The 2010 Index of Multiple Deprivation (IMD) [38] is one of the most commonly used indicators of deprivation and the one used in the NCMP. It combines a number of indicators, chosen to cover a range of economic, social and housing issues, into a single deprivation score for each small area in England. Schools will be stratified into low, medium and high IMD tertiles (based on school postcode) by the study team. These data will be provided to the Newcastle Clinical Trials Unit and a statistician, independent to the study team, will randomly allocate the stratified schools in a block design.

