#### Anthropometry

Child’s height and weight at baselineChild’s height and weight at 12 month follow-upParents’ weight status based on self-reported height and weight measures

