### Sample size

The required sample size is based on detecting a difference in a dichotomous outcome. There are two intervention groups and a control group; the primary comparisons of interest will be between each of the intervention groups and the control group. To take into account the multiple comparisons, the type 1 error rate is specified as 2.5 %. The unit of randomisation is the school.

We estimate the number of eligible children per school completing the study to be 15. This is based on the assumptions that we will survey 120 children per school (2 classes of 30 in each of the two year groups). Of these children we anticipate that 40 (33 %) will meet the study analysis entry criteria (i.e. be overweight) and that of these 20 (50 %) will agree to participate and that of these we will be able to collect follow up data at 12 months for 15 (75 %).

The study is estimated to have 90 % power to detect a 20 point difference between the control group and each of the intervention groups at one month (that is, 30 % of parents accurately perceiving their overweight child as overweight versus 50 %). Applying Fleiss’s method for a proportion incorporating a continuity correction, we would need a final sample size of 471 overweight children (three groups of 157). With an assumed intra-cluster correlation coefficient of 0.01 and a mean cluster size of 15, the design effect is 1 + 14*0.01 = 1.14 implying that we need a final sample size of at least 537 children and thus we will need a minimum of 36 schools. With 120 children per school this will provide a sampling frame of 4320 children. The target sample size is 2160 parent–child pairs.

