### Statistical analysis

Analysis will be restricted to the parents of the overweight children. For the primary outcome measure (dichotomous variable based on correct/incorrect perception of weight status) the null hypothesis is that there is no difference in the proportion of parents with the correct perception of child body weight status between individuals in the control or intervention groups. This will be tested using a logistic multilevel model to account for clustering at school level using specialist statistical software such as MLwiN [41]. Using a multilevel modelling approach will also allow variation in change in perception to be partitioned in to school, year group and individual levels and will permit the inclusion of characteristics of individuals (IMD) and schools (Free School Meal Index and IMD) and anthropometric measures for both child and parent. Inclusion of such terms may reduce the estimate of the standard deviation for the effect and hence provide a more precise estimate of the effect of the intervention. A continuous variable of perception of the child’s weight based on the VAS is also a primary outcome measure.

The secondary outcome measures include knowledge of the consequences of childhood overweight, intention to change lifestyle behaviours and/or seek advice, perceived control, action planning, coping planning, seeking support behaviours, and the child’s body weight status at 12 month follow-up. Process evaluation will use the same statistical approach to test group differences on any of the psychological secondary outcomes.

Although a formal economic analysis is not part of this trial, the study team will work with health economists and use our existing knowledge of the literature to consider the economic implications of our findings.

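### The primary model may adjust for parents' self-reported weight, apparently collected after Map Me exposure, while the randomisation stratifier (school IMD tertile) is only optional

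*Protocol article*

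**What the plan says.** The Statistical analysis section tests the primary outcome, correct or incorrect perception among parents of overweight children, with a logistic multilevel model. It says this approach permits individual IMD and a further group of terms, "Free School Meal Index and IMD) and anthropometric measures for both child and parent", because such terms may make the effect estimate more precise. No term is compulsory.

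The Anthropometry section defines the parent measure as "weight status based on self-reported height and weight measures" and gives no time for it.

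The Procedure section describes one study questionnaire and says that "the questionnaire consists of the outcome and explanatory measures". Controls are posted it soon after their consent forms arrive. Intervention parents are posted it once the four-week Map Me period has ended. The only later questionnaire is at 12 months.

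On allocation, the Randomisation of schools section says "Schools will be stratified into low, medium and high IMD tertiles", with random allocation in blocks within that stratification.

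**The concern.** The precision argument for covariates holds when they are fixed before exposure, or cannot be changed by it. Parent self-reported height and weight does not clearly meet that condition. On the procedure described, it is reported after a month with a weight-awareness tool in two arms and without exposure in the third.

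Map Me could plausibly change how parents report their own weight, or whether they report it. The item also appears to share a form with the outcome, so a general readiness to acknowledge overweight could drive both answers. Adjusting for such a variable can remove part of the intervention effect or create an association that randomisation had excluded. At stake is the validity of the primary comparison if this term is used.

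The second part is smaller. Schools are randomised within IMD tertiles, but the model need not contain them. The analysis may then give up precision that the design has already secured.

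**Working it through.** **1. The plan's own figure.** Inputs, all from Sample size: "the type 1 error rate is specified as 2.5" per cent; "90 % power to detect a 20 point difference between the control group and each of the intervention groups at one month"; "30 % of parents accurately perceiving their overweight child as overweight versus 50" per cent. Sidedness is not stated; two-sided reproduces the result.

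- n0 = [2.241·√(2·0.4·0.6) + 1.282·√(0.3·0.7 + 0.5·0.5)]² / 0.2² = 146.7
- With continuity correction: n = (n0/4)·[1 + √(1 + 4/(n0·0.2))]² = 156.5, so 157 per arm
- 3 × 157 = 471, matching "we would need a final sample size of 471 overweight children (three groups of 157"
- Design effect 1 + 14 × 0.01 = 1.14; 471 × 1.14 = 536.9, so 537; 537/15 = 35.8, so 36 schools

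The sample size reproduces and contains no covariates. This point does not change it.

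**2. When the parent measure is taken.**

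| | Control | Paper and web Map Me |
|---|---|---|
| Consent form | before randomisation | before randomisation |
| Map Me | none | four weeks |
| Study questionnaire | soon after consent | after the four weeks |

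Apart from the consent form, no data collection from intervention parents before exposure is described. The parent measure is therefore most naturally read as post-exposure in both intervention arms. This is an inference: the article does not list the explanatory measures, and collection at consent is not excluded.

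**3. What adjustment could do.** Let exposure shift the reported covariate by d, and let the covariate have log-odds slope b on the outcome. Then, approximately,

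adjusted log odds ratio = unadjusted log odds ratio − b·d.

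If d = 0 there is essentially no bias. Otherwise the sign is that of −b·d, and the documents give neither b nor d.

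A simulation illustrates this. It used 400,000 parents per scenario, the plan's 30% and 50% as the outcome model, and an assumed unmeasured readiness to label weight that affects both the report and the outcome.

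| Assumed rise in parents reporting overweight | Unadjusted odds ratio | Adjusted odds ratio |
|---|---|---|
| none | about 2.1 | 2.11 to 2.16 |
| 4 to 5 points | about 2.1 | about 2.09 |
| 8 to 10 points | about 2.1 | about 2.02 |
| 16 to 19 points | about 2.1 | about 1.93 |

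The assumed signs of b and d were both positive here. Opposite signs would move the estimate the other way.

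**4. The stratifier.** Suppose school-level terms explained all between-school variation. The variance would then fall by at most the design effect, so on this approximation the standard error falls by at most 1 − 1/√1.14 = 6.3%. With 20 per school, the number of participants before 12-month losses, the design effect is 1.19 and the bound is 1 − 1/√1.19 = 8.3%. IMD tertile alone would explain less than all of that variation, so the real gain is smaller.

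**The case against.** The strongest reply is that the article fixes no covariate set. It says what a multilevel model permits, and a condensed article properly leaves the final specification to an analysis plan. That stands against any complaint that the list is open, or that terms could be chosen after seeing results; nothing shown supports that charge. It does not answer the main point. The article names an unsuitable term for the primary model and justifies it by a rationale that does not fit it, and an analysis plan that follows the text would inherit the problem. School IMD is also named, so the stratifier is not overlooked, only not required.

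The reply on timing stands in part. Parent weight could be collected on the consent form; if so, one sentence settles the matter. The mechanism is plausible but not shown. Only the web version projects an adult body image, and that image is the child's. Neither format is described as addressing the parent's own weight.

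A reader might infer more than the documents support:

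- **That the item will often be blank and power will fall to 77%.** No missing-data rate is given. With 12 schools per arm, m children per school and effective n = 12m/[1 + (m − 1)·0.01], assumed blanks of 0, 10, 20 and 30% from m = 15 give power of 90, 87, 83 and 77%. But 15 is the count with 12-month data, and the primary outcome is at one month. Starting from the 20 participants, an upper bound, the same blanks give 96, 95, 92 and 88%.
- **That the odds ratio would be inflated to about 2.55.** The planned odds ratio is (0.5/0.5)/(0.3/0.7) = 2.33. With b·d = 0.3 × 0.3 = 0.09 in absolute value, it becomes 2.33 × e^0.09 = 2.55 or 2.33 × e^−0.09 = 2.13, according to sign. Both inputs are invented.
- **That year group is wrongly treated as a level.** Year groups nested in schools are an ordinary variance partition, and nothing excludes a fixed effect as well. That is a preference.

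**Conclusion.** The point holds in a limited form. The plan allows the primary model to adjust for a parent self-report that, on the procedure described, follows exposure in both intervention arms and precedes any exposure in control. The possible bias has unknown sign and size, and is essentially nil if Map Me does not alter the report. Any loss of parents through blanks is real only if the term is used in a complete-case fit, and cannot be sized from the article. The conclusion rests on the item being in the study questionnaire and not on the consent form.

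Leaving out school IMD tertile does not bias the comparison. It makes the standard error slightly too large: at most about 6% at the plan's cluster size of 15 and ICC of 0.01. Both parts are worth correcting, because the change is easy and removes a doubt about the primary result.

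**What to change.** In Statistical analysis, require school IMD tertile in the primary model. Limit any other primary-model covariates to those measured before exposure or not affected by it, for example residential IMD, year group and NCMP-measured child BMI. Use parent self-reported weight status only in a labelled exploratory analysis, unless it is collected before exposure. In Anthropometry, state when parents' height and weight are reported.

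The cost is wording only. The terms named are already collected or available, and the sample size is unchanged.

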**Design:**

This cluster randomised trial will test the effectiveness of the Map Me intervention. Primary schools will be randomised to: paper-based Map Me; web-based Map Me; no information (control). Parents of reception (4–5 years) and year 6 (10–11 years) children attending the schools will be recruited. The study will work with the National Child Measurement Programme which measures the height and weight of these year groups and provides feedback to parents about their child’s weight status. Before receiving the feedback, parents will complete a questionnaire which includes assessment of their perception of their child’s weight status and knowledge of the health consequences of childhood overweight. The control group will provide pre-intervention data with assessment soon after recruitment; the intervention groups will provide post-intervention data after access to Map Me for one month. The study will subsequently obtain the child height and weight measurements from the National Child Measurement Programme. Families will be followed-up by the study team at 12 months. The primary outcome is any difference in accuracy in parental perception of child weight status between pre-intervention and post-intervention at one month. The secondary outcomes include differences in parent knowledge, intention to change lifestyle behaviours and/or seek advice or support, perceived control, action planning, coping planning, and child weight status at 12 month follow-up.

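### The 2.5% level uses up the 5% on one dichotomous outcome, yet the VAS is named as a further primary outcome with no rule for testing it

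*Protocol article*

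**What the plan says.** All references are to the protocol article.

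- **Sample size**, outcome: "The required sample size is based on detecting a difference in a dichotomous outcome".
- **Sample size**, comparisons: "the primary comparisons of interest will be between each of the intervention groups and the control group".
- **Sample size**, error rate: "To take into account the multiple comparisons, the type 1 error rate is specified as 2.5" per cent.
- **Sample size**, power: "The study is estimated to have 90 % power to detect a 20 point difference between the control group and each of the intervention groups", taken as 30% versus 50% at one month.
- **Statistical analysis**, first primary outcome: "For the primary outcome measure (dichotomous variable based on correct/incorrect perception of weight status"). A null hypothesis and a multilevel logistic model are attached to it.
- **Statistical analysis**, last sentence of the same paragraph: "A continuous variable of perception of the child’s weight based on the VAS is also a primary outcome measure".

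Nothing in the article says how the two primary outcomes combine into a conclusion about the intervention.

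**The concern.** The reason given for the 2.5% level is multiple comparisons, and the only comparisons named are the two arms against control. Halving 5% for two comparisons leaves nothing for a second primary outcome. Two outcomes and two comparisons make four primary tests, twice the number that the adjustment covers.

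What follows depends on how success is defined, and the article does not say. If a positive result on either outcome is enough, the chance of at least one false primary claim is above the 5% that the 2.5% level was chosen to protect. If both outcomes must be positive, that chance is controlled, but the power statement then describes only one of two necessary conditions. Under either rule, one of the stated design properties does not extend to the primary outcomes as declared. The harm would show if the two outcomes disagreed. A result positive on the VAS alone could be reported as a primary finding, with no agreed rule for or against doing so.

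**Working it through.** **1. Reproduce the planned size.** Inputs from Sample size: 30% versus 50%, 90% power, level 2.5%, Fleiss's method with continuity correction. Sidedness is not stated, so I take two-sided.

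- z for two-sided 2.5% = 2.2414; z for 90% power = 1.2816; mean proportion 0.40; difference d = 0.20.
- Uncorrected: n' = [2.2414 × √(2 × 0.4 × 0.6) + 1.2816 × √(0.3 × 0.7 + 0.5 × 0.5)]² / 0.20² = (1.553 + 0.869)² / 0.04 = 146.7.
- Corrected: n = (n'/4) × [1 + √(1 + 4/(n'd))]² = 36.67 × (1 + 1.066)² = 156.5, so 157 per group.
- 3 × 157 = 471; 471 × 1.14 = 536.9, so 537; 537/15 = 35.8, so 36 schools.

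All four figures match the article. Two-sided 5%, or one-sided 2.5%, would give 134 per group. So the 2.5% is a two-sided level per comparison, and 2 × 2.5% = 5% is fully committed to the dichotomous outcome.

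**2. Family-wise error for the dichotomous outcome alone.** With 1:1:1 allocation, the two comparisons share the control arm, so their test statistics have correlation 0.5. Simulation of two correlated normal statistics, each tested two-sided at 2.5%, gives 0.0465, reported here as 4.6%. The adjustment works for the outcome it was built for.

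**3. Family-wise error for four tests, if either outcome can carry the claim.** Bonferroni bound: 4 × 2.5% = 10%. The model is four normal statistics with correlation 0.5 between comparisons, r between outcomes, and 0.5 × r across both (4 million draws). The article gives no value for r, so it is an assumption shown over a range.

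| r between outcomes | Family-wise error |
|---|---|
| 0 | 9.1% |
| 0.5 | 8.5% |
| 0.7 | 7.9% |
| 0.8 | 7.4% |
| 0.9 | 6.7% |
| 0.95 | 6.1% |
| 0.98 | 5.6% |
| 1 | 4.6% |

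Check at r = 0: 1 − (1 − 0.0465)² = 0.091, which agrees. The rate returns below 5% only when r is almost 1.

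**4. If both outcomes must succeed.** For a given intervention, a false claim needs at least one test with a true null to be significant at 2.5%. Over two interventions the total is therefore at most 2 × 2.5% = 5%. Joint power cannot exceed the 90% of the dichotomous test, and falls below it whenever the VAS can fail when the dichotomous test succeeds. The article gives no VAS difference, standard deviation or power, so joint power cannot be computed.

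**5. If the 5% were split four ways.** Each test gets 5%/4 = 1.25% two-sided. At 157 per group, power on the dichotomous outcome falls from 90% to about 85% (0.848). Restoring 90% needs 179 per group; 3 × 179 = 537 before clustering; 537 × 1.14 = 612.2, so 613 children; 613/15 = 40.9, so 41 schools. (The 537 here is before the design effect and matches the planned total only by coincidence.)

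**6. If the VAS is gated on the dichotomous outcome within each intervention.**

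- If the dichotomous null is true for an intervention, any false claim for it must first pass that test, with probability at most 2.5%.
- If the dichotomous null is false and the VAS null is true, the only possible false claim is the VAS test, again at most 2.5%.
- Summed over two interventions: at most 5%. The dichotomous test keeps its 2.5% level and so its planned power.

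**The case against.** The strongest reply is that the article already shows which outcome leads. The dichotomous variable carries the null hypothesis, the model, the sample size and the first stated aim; the VAS has one closing sentence. On that reading the word primary is a loose label for a supporting measure, and any testing order may sit in an analysis plan that is not shown. Part of this stands. The absence of a decision rule would not be a finding by itself, and the dichotomous analysis is unaffected. It does not remove the point, because the article itself fixes both the error rate, with its reason, and a second primary outcome, and the two do not fit together.

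Four stronger readings are tempting, and the article does not support them.

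- **That the family-wise error simply exceeds 5%.** This needs an either-outcome rule, which the article neither states nor excludes. The 9.6% from 1 − 0.975⁴ also assumes independent tests, which the shared control rules out.
- **That the VAS rewards any upward shift and so cannot measure accuracy.** The Measures section describes a 10 cm line with labelled ends, and Statistical analysis speaks only of a continuous variable based on it. Scoring is not fixed there, and nothing says that a higher mark counts as better.
- **That a single global null replaces the two pairwise ones.** The wording of the null is loose, but Sample size names the pairwise comparisons as the primary ones.
- **That the abstract contradicts the main text by naming one primary outcome.** Its wording is "The primary outcome is any difference in accuracy in parental perception of child weight status between pre-intervention and post-intervention at one month". This describes a construct, and the Measures section lists both the questionnaire item and the VAS as assessments of the child's weight status. I place no weight on it.

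**Conclusion.** The point holds as a mismatch between two things the article states: an error rate that covers two tests on one outcome, and a declaration of two primary outcomes.

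Its size is conditional. If either outcome suffices, the family-wise error is about 6% to 9% for assumed outcome correlations from 0.95 down to 0, with a bound of 10%, against 4.6% for the dichotomous outcome alone. Two measures from the same parent on one questionnaire may well be strongly correlated, so the lower part of that range deserves as much attention as the upper. If both outcomes are required, the error is controlled and the gap is in the power claim. The figures rest on two-sided tests at 2.5%, equal arms and large-sample normal statistics.

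A reader might infer that the primary analysis as a whole is unsound. It is not: the dichotomous comparisons, their level and their sample size are coherent and reproduce exactly. This is a should-fix point.

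**What to change.** State that the dichotomous outcome, on which the trial is sized, is the single primary outcome, tested for each intervention against control at two-sided 2.5%. State that, for each intervention, the VAS is tested at 2.5% only if that intervention is significant on the dichotomous outcome. Otherwise the VAS is reported as an estimate with its confidence interval and supports no confirmatory claim. Record the change before outcome data are analysed.

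The cost is that the VAS loses its stand-alone primary status. That is a real change to a declared outcome, not merely an edit of wording. The stated power, the sample size and the number of schools stay as they are.

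If the VAS is to remain a full primary outcome, two alternatives also control the error. A four-way split at 1.25% lets either outcome carry a claim, but power on the dichotomous outcome at the planned size drops to about 85% and should be restated, or the size raised to 179 per group (613 children, 41 schools). A both-must-succeed rule keeps 2.5% per comparison but needs a power calculation for the VAS and for the two outcomes jointly. The article should state one of these rules.

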Data on how parents’ perceptions of their child’s weight status can be improved are limited. The National Child Measurement Programme (NCMP) currently measures height and weight of school children in reception (age 4–5 years) and year 6 (age 10–11 years) in maintained schools, that is all but special needs and fee-paying schools, in England. These data are used to calculate each child’s body mass index (BMI): an index of overall body fat based on height and weight (BMI = weight[kg]/height^2^[m]). The BMI scores are converted to age and sex specific centiles calculated using the British 1990 growth reference UK90 [8] to determine the number of children defined as underweight, healthy weight, overweight or obese as a proportion of the number measured. Children are classified as ‘underweight’ if they have a BMI below the 2^nd^ centile; as ‘healthy weight’ between the 2^nd^ and 90^th^ centiles; as ‘overweight’ between 91^st^ and 97^th^ centiles; and as ‘very overweight’ at or above the 98^th^ centile. These results are typically communicated to parents within six weeks of measurement by letter which informs them of their child’s BMI and the UK90 category into which this falls, usually with a Change4Life leaflet (a public health programme to tackle obesity in England, and run by the Department of Health) and information on local services. Evaluations of the letters indicate that they are often not well received by parents of overweight children who doubt the veracity of the assessments, and therefore may fail to promote appropriate action [9, 10]. Similarly, the growth chart is regularly used to monitor children’s growth and to educate families about the growth process. However, the usefulness of these charts depends on whether parents are able to understand them and existing evidence shows that the general population does not [11]. Other approaches may therefore be more effective than teaching parents mathematical concepts [12].

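### The 12-month child outcome is named only as weight status, a category in this protocol; naming baseline-adjusted BMI SDS would keep substantial information already collected

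*Protocol article*

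**What the plan says.** The 12-month child outcome appears in three places: the Design part of the Abstract, the aims at the end of the Background, and Statistical analysis. Each time it is called weight status. Statistical analysis gives it as "seeking support behaviours, and the child’s body weight status at 12 month follow-up". No BMI, centile or BMI SDS outcome is named anywhere.

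The Background explains where weight status comes from. "The BMI scores are converted to age and sex specific centiles calculated using the British 1990 growth reference UK90", and the centiles are then cut into bands, the upper two being "as ‘overweight’ between 91^st^ and 97^th^ centiles; and as ‘very overweight’ at or above the 98^th^ centile". The body image scales (Intervention) and the parental questionnaire item (Measures) also use bands.

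Two other statements bear on the point. Statistical analysis says "Analysis will be restricted to the parents of the overweight children". At 12 months, according to Procedure, "the children will be measured for height and weight by the study team, usually at school"; Anthropometry lists height and weight at baseline as well.

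The sample size concerns parental perception only: "90 % power to detect a 20 point difference between the control group and each of the intervention groups at one month". No target difference, model or power is given for 12-month child weight.

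**The concern.** Every analysed child starts at or above the 91st centile. A categorical outcome changes only when a child crosses the 91st or the 98th centile (SDS 1.341 and 2.054). A child who moves from SDS 1.9 to 1.5, or from 2.8 to 2.3, improves clearly and is recorded as unchanged. BMI on a continuous scale, adjusted for its strongly predictive baseline value, uses the movement of every child.

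This is the only listed outcome that shows whether the tool affects children's weight, which is one of the stated aims. If it is analysed as a category, a modest but real shift in BMI could be missed, and the null result could be read as no effect on weight. The better variable can be derived from data the trial already collects.

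**Working it through.** **1. The plan's own figure.** Inputs from Sample size: "30 % of parents accurately perceiving their overweight child as overweight versus 50" per cent, 90% power, and "To take into account the multiple comparisons, the type 1 error rate is specified as 2.5" per cent (taken as two-sided, since this reproduces the stated number).
- Uncorrected: n = [2.241·√(2·0.4·0.6) + 1.282·√(0.3·0.7 + 0.5·0.5)]² / 0.2² = 146.7.
- With continuity correction: (146.7/4)·[1 + √(1 + 4/(146.7·0.2))]² = 156.5, so 157 per group and 471 in total.
- Clustering: 471 × 1.14 = 536.9, so 537 children; 537/15 = 35.8, so 36 schools.

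All of this agrees with the article.

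**2. Numbers available at 12 months.** 36 schools × 15 children = 540, or 180 per arm. Dividing by the design effect gives 180/1.14 = 158 effective children per arm. This assumes that the ICC of 0.01 stated for the primary outcome also holds for BMI.

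**3. Assumptions not in the document.** Baseline BMI SDS is normal with mean 0.6 and SD 1.1, truncated at the 91st centile, so overweight is taken to include very overweight. The 12-month SDS equals baseline plus a normal change with SD 0.4, minus a uniform shift in the intervention arm. Each test is two-sided at 2.5%.

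**4. Simulated power for four analyses of the same data.**

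| Shift in BMI SDS | Overweight yes/no, unadjusted | Yes/no, adjusted for baseline | Three-category score, adjusted | BMI SDS, adjusted |
|---|---|---|---|---|
| 0.10 | about 13% | about 16% | about 28% | about 49% |
| 0.15 | about 29% | about 35% | about 61% | about 86% |
| 0.30 | about 90% | over 90% | over 90% | near 100% |

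Repeated runs differ by one to three percentage points; for adjusted yes/no at 0.15 they gave 35% to 38%. At a 0.15 shift, changing the SD of change to 0.3 or 0.5 moves unadjusted yes/no to about 40–44% or 22–24%, and adjusted BMI SDS to about 99% or 66%.

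**5. Sensitivity to the baseline distribution.** The distribution in step 3 puts 25% of children above the 91st centile, whereas Sample size expects 33% to be overweight. A second set of simulations fixed that share at 33%, with population SD 1.1 to 1.3 and a baseline to 12-month correlation of 0.80 to 0.95. Power at a 0.2 shift:

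| Analysis | Central case (SD 1.2, correlation 0.9) | Range |
|---|---|---|
| Yes/no, unadjusted | 36% | 23–60% |
| Yes/no, adjusted | 47% | 27–75% |
| Three-category score, adjusted | 67% | 38–93% |
| BMI SDS, adjusted | 87% | 53–100% |

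**6. Information kept.** This is the squared ratio of each analysis's mean test statistic to that of adjusted BMI SDS, in the second set. Unadjusted yes/no keeps about 21–44%, adjusted yes/no 28–52%, and the adjusted three-category score 50–73%.

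**The case against.** The strongest reply is that the article does not fix a categorical analysis. It gives no scale, cut-off or model for this outcome, and a condensed article may leave these to the full protocol or analysis plan. The term is also used more loosely in places: Measures puts a continuous visual analogue scale under parental assessment of weight status, the aims speak of outcomes in the plural, and Anthropometry lists height and weight, not bands. This stands, and it limits the point to the variable named. It does not remove the point, because an outcome variable is named and the only definition given for it is categorical.

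A reader might go further and infer that the outcome is simply whether the child is still overweight, that most of the information is discarded, that power is low, and that a real effect would most likely be reported as none. The documents do not support that reading:
- The 98th-centile boundary allows movement between overweight and very overweight, so a yes/no split is not stated.
- A three-category score adjusted for baseline keeps half or more of the information.
- Statistical analysis allows anthropometric covariates. It does so in describing the perception model, so baseline BMI is neither tied to the 12-month outcome nor excluded from it.
- Power depends on an effect and an SD that the article does not give. At 0.30 SDS even the weakest analysis reaches about 90%.
- The outcome is secondary, and no power is claimed for it.

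**Conclusion.** The point holds in limited form. The 12-month child outcome is named only as weight status, which this protocol defines by UK90 category, and the analysed children are all overweight at baseline. Analysed as a category, it would lose substantial information relative to BMI measured at both times: roughly a quarter to a half with three categories and baseline adjustment, and about half to four fifths with a yes/no split.

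The ordering of the four analyses was the same under both sets of assumptions, apart from ties where power is near complete. The absolute power figures rest on the assumed shift, SD of change, baseline distribution and ICC, and should be read as illustration only. Nothing here affects the primary outcome or its sample size, which reproduces exactly.

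**What to change.** In Statistical analysis, and in the matching aim in the Background, name UK90 BMI SDS at 12 months as the child weight outcome. Analyse it in a linear multilevel model with baseline BMI SDS as a covariate and school as a random effect. Report weight-status category alongside as supportive. If the unseen analysis plan already does this, the article's wording only needs to be aligned with it.

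The cost is a change of wording, since both measurements are already collected. The one drawback is that SDS is less familiar to lay readers, which reporting the categories alongside addresses.
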